## Abstract

**Background:** Parkinson’s disease (PD) is a neurodegenerative movement disease that includes non-motor symptoms such as cognitive impairment. Long-term mind-body exercise has been shown to improve cognitive ability in PD patients, but the methods of assessment and intervention were inconsistent across studies. Wuqinxi is a mind-body exercise that is easy to learn, has few physical and cognitive demands, and is recommended for PD patients. Dynamic functional connectivity (DFC) has been associated with cognitive alterations in PD patients, but no studies have yet explored the effects of Wuqinxi on this association. The current protocol is designed to measure the effects of long-term Wuqinxi intervention on cognition in PD patients, and explore the underlying neural mechanisms through DFC.

**Methods:** A long-term single-blind, randomized trial will be conducted. PD patients and age- and gender-matched HC will be recruited; PD patients will be randomly assigned to either Wuqinxi or balance groups, and HC will all receive health education. The Wuqinxi group will receive a 90-min session of Wuqinxi intervention three times a week for 24 weeks, while the balance group will receive balance exercise instruction on the same schedule. Primary outcomes will include assessment of cognitive domains and dynamic temporal characteristics of functional connectivity. Secondary outcomes will include severity of motor symptoms, mobility, balance, and emotional state. Assessments will be conducted at baseline, at the end of 24 weeks of intervention, and 12 weeks after interventions have ended.

**Discussion:** This study will provide evidence to the effects of Wuqinxi exercise on cognitive improvements in PD patients from the perspective of DFC, and will contribute to the understanding of neural mechanisms underlying cognitive enhancement through Wuqinxi practice.

**Clinical Trial Registration:**www.chictr.org.cn, identifier ChiCTR2000038517.

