### Sample Size Calculation and Blinding

Sample size estimation was performed by G^∗^power V3.1 software (Franz Faul, Universitat Kiel, Germany). According to the analysis, at least 44 participants should be recruited (22 participants per group) in order to be able to perform two-factor repeated ANOVA (within-between interaction) with a middle effect size of 0.25 (Cohen, 1988), level of significance of 0.05, and power of 95% (Mayr et al., 2007). Since some participants may need to be dropped from the analysis due to excessive head motion during scanning, 40 participants will be recruited for each PD subgroup and 40 HC will be recruited. According to a similar studies published recently (Fiorenzato et al., 2019; Chen et al., 2021), this sample size should be adequate for replicating the previous effects in Fiorenzato’s study. In order to attract more participants, we will offer generous compensation and long-term health guidance. Every participant will be offered with an individual exercise plan when the whole study was completed. Randomization of PD patients will be done at the website www.random.org. Two researchers will be trained to assess the outcomes, and they will be blinded to group and will not participate in any interventions.

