#### Primary Outcome Assessment

The Montreal Cognitive Assessment (Nasreddine et al., 2005) will be conducted to assess cognitive impairment and the Repeatable Battery for the Assessment of Neuropsychological Status (Stella et al., 2013) will be used to measure the cognitive domains of immediate memory, visuospatial, language, attention, and delayed memory (see Supplementary Table 1). Dynamic states, dwell times, fractional windows, and number of transitions will be computed to reflect the characteristics of DFC (see Supplementary Table 1).

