#### Application of DFC in Wuqinxi Intervention

##### Clinical and neuropsychological data analysis

Statistical analyses will be performed using SPSS version 19.0. Demographic and clinical information of two PD subgroups (wuqinxi group vs. balance group) will be compared across the three timepoints (baseline, 24 weeks, and 12-week follow-up) using two-factor repeated analysis of variance (ANOVA), see Table 1. Pearson’s chi-square test will be used to compare categorical variables (see Table 1). Pearson’s correlation analyses will be applied between temporal properties and cognition (MoCA and cognitive performance in each domain) across two PD subgroups as well as motor severity (UPDRS-III) before the intervention (see Table 2). Then, the same correlation analyses will be used after the intervention and will also be carried out after follow-up (see Table 2). The threshold for statistical significance will be set at *p* < 0.05.

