##### Group differences in dynamic connectivity: temporal and properties and strength

Between-group (wuqinxigroup vs. balance group) differences in dwell time, fractional windows, and number of transitions will be examined using two-factor repeated ANOVA (*p* < 0.05, FDR correction), see Supplementary Table 1. Covariates will include education, levodopa and dopamine agonist equivalent daily doses. Continuously, subject-specific medians corresponding to each group-level state will be estimated and two-factor repeated ANOVA will be used to compare the connectivity strength of each state at each unique regional pairing (*p* < 0.05, FDR correction) between the three timepoints (before intervention, after intervention, and follow-up), see Supplementary Table 1. Finally, two-factor repeated ANOVA will be performed to compare strength abnormalities associated with cognitive deficits by comparing different timepoints of Wuqinxi group and balance group (*p* < 0.05, FDR correction), see Supplementary Table 1.

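### Six co-equal primary cognitive scores are given a plain 0.05 threshold with no correction stated, while the dynamic connectivity measures get FDR correction

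*Protocol article*

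**What the plan says.** The Abstract puts cognition and connectivity side by side: "Primary outcomes will include assessment of cognitive domains and dynamic temporal characteristics of functional connectivity". *Primary Outcome Assessment* lists the MoCA, and the RBANS, which "will be used to measure the cognitive domains of immediate memory, visuospatial, language, attention, and delayed memory". That makes six cognitive scores. None is named as the lead, and no order is given.

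Under *Application of DFC in Wuqinxi Intervention*, the subsection on clinical and neuropsychological data compares the two PD groups over the three visits by two-factor repeated ANOVA. It then describes correlations between connectivity and cognition, and closes with "The threshold for statistical significance will be set at" p < 0.05. No correction is mentioned.

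The subsection that follows states that "differences in dwell time, fractional windows, and number of transitions will be examined using two-factor repeated ANOVA" with p < 0.05 and FDR correction. It repeats the FDR condition for its other two comparisons, the last ending "FDR correction), see Supplementary Table 1". The PD versus healthy control analysis has the same pattern: a plain 0.05 for clinical and neuropsychological data, and FDR three times for DFC.

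*Sample Size Calculation and Blinding* plans a within-between interaction "with a middle effect size of 0.25", at significance level 0.05 and 95% power. It reaches 44 patients and recruits 40 per PD group.

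**The concern.** Six primary scores, each judged at 0.05, give six chances of a nominal finding on the outcome the trial is meant to inform. The article deals with multiplicity for the imaging measures but not for the cognitive ones, and gives no reason for the difference. The clinical outcome is therefore held to a looser standard than the mechanistic one. Naming cognition as the family that decides the trial would not help, because the multiplicity lies inside that family.

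**Working it through.** **Inputs from the article.** Six cognitive scores (MoCA plus five RBANS domains); threshold 0.05; two groups, three visits; f = 0.25; power 95%; minimum N = 44; 80 PD patients recruited.

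**Assumptions, not in the article.** One group-by-time test per score. Equal correlation between scores, varied from 0 to 0.7. For power, a correlation of 0.5 among repeated measures and epsilon = 1.

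**Step 1: the plan's own sample size.** The interaction F test has λ = f² × N × m / (1 − ρ), df1 = (k − 1)(m − 1) and df2 = (N − k)(m − 1), with k = 2 groups and m = 3 visits. At N = 44, λ = 0.0625 × 44 × 3 / 0.5 = 16.5 with 2 and 84 degrees of freedom, and power at 0.05 is 95.6%. The figure of 44 is reproduced, for one test at 0.05.

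**Step 2: false-positive rate across six null tests.** If independent, 1 − 0.95⁶ = 26.5% in either direction. In a fixed direction, 1 − 0.975⁶ = 14.1%. Correlated scores were simulated in two ways: as two-sided z tests (400,000 draws), and as the actual 2 × 3 interaction test with 40 per group (40,000 trials).

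| Between-score correlation | Any difference, z tests | Any difference, interaction test | Favours Wuqinxi, z tests | Interaction significant and 24-week change favours Wuqinxi | Interaction significant and either later visit favours Wuqinxi |
|---|---|---|---|---|---|
| 0 | 26.5% | 27.0% | 14.1% | 14.5% | 18.9% |
| 0.3 | 24.0% | 24.1% | 12.1% | 12.5% | 16.5% |
| 0.5 | 20.7% | 21.2% | 10.3% | 11.0% | 14.6% |
| 0.7 | 16.4% | 16.9% | 8.2% | 8.8% | 11.6% |

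For a single test in a fixed direction the rate is 0.05 / 2 = 2.5%. The six-score rate is therefore 14.1 / 2.5 = 5.6 times that if the scores are independent, and 8.2 / 2.5 = 3.3 times at correlation 0.7.

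**Step 3: what correction costs.** The strictest Holm step is 0.05 / 6 = 0.0083. If all six tests used that level and were independent, the family-wise rate would be 1 − (1 − 0.0083)⁶ = 4.9%. Power for one score at that step, from the formula in step 1:

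| Patients analysed | λ | Power at 0.0083 |
|---|---|---|
| 44 | 16.5 | 84.1% |
| 60 | 22.5 | 95.4% |
| 80 | 30.0 | 99.2% |

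**The case against.** **The ANOVA is not explicitly tied to the six scores.** Its sentence covers demographic and clinical data and points to Table 1, which lists neither MoCA nor RBANS. The section names these scores only in the correlations, just before the 0.05 sentence. This stands as a limit on the wording. The inference is still strong: the heading says neuropsychological, the three visits match the outcome schedule, and the sample size section plans this same interaction test. If the section did not cover the six scores, the article would state no between-group test for them at all.

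**The article is condensed, and an SAP may settle multiplicity.** This would be decisive if the article said nothing on the subject. But it sets a threshold for this analysis and adds a correction only to the neighbouring ones, in both parts of the analysis section. It does not use the word uncorrected, so the fair description is that no correction is stated.

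**A reader might infer a 16-26% chance of falsely claiming cognitive benefit.** The article does not support that. Those figures count differences in either direction, including ones favouring balance training. Nor does the article give a success rule under which one nominal result would be reported as improvement; its stated aim is to explore effects.

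**Correction may cost more than it seems.** This stands in part. Recruitment was raised to allow for head motion, and patients who move more than 1 mm are to be removed from the study, so fewer than 80 may be analysed.

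**Conclusion.** The point holds as an inconsistency in the stated thresholds with a measurable effect. Under the inferred reading, the chance of at least one false-positive cognitive group-by-time difference is about 26% with independent scores and 16-17% at correlation 0.7. In favour of Wuqinxi it is about 14% to 8% with a fixed direction, or about 19% to 12% if a favourable change at either later visit counts. The between-score correlations are assumptions, and the article gives no value from which to narrow the range. The finding does not show that the authors chose to leave these tests uncorrected, or that a single nominal result would be claimed as benefit.

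**What to change.** In the clinical and neuropsychological subsection of *Application of DFC in Wuqinxi Intervention*, state that the group-by-time tests of the MoCA and the five RBANS domains form one family, corrected by Holm or at least by the FDR rule already applied to the DFC measures. The same sentence should say that the two-factor repeated ANOVA is the test for these six scores. It should be settled before any group comparison is seen.

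The cost is a stricter threshold per score. At f = 0.25 and under the power assumptions above, the 95% target survives the strictest Holm step only if about 60 or more patients are analysed, that is, if no more than about 20 of the 80 are lost. At the stated minimum of 44, power at that step falls from 95.6% to 84.1%.

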##### Group differences in dynamic connectivity: temporal and properties and strength

Between-group (wuqinxigroup vs. balance group) differences in dwell time, fractional windows, and number of transitions will be examined using two-factor repeated ANOVA (*p* < 0.05, FDR correction), see Supplementary Table 1. Covariates will include education, levodopa and dopamine agonist equivalent daily doses. Continuously, subject-specific medians corresponding to each group-level state will be estimated and two-factor repeated ANOVA will be used to compare the connectivity strength of each state at each unique regional pairing (*p* < 0.05, FDR correction) between the three timepoints (before intervention, after intervention, and follow-up), see Supplementary Table 1. Finally, two-factor repeated ANOVA will be performed to compare strength abnormalities associated with cognitive deficits by comparing different timepoints of Wuqinxi group and balance group (*p* < 0.05, FDR correction), see Supplementary Table 1.

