### Resting-State and Structural MRI Acquisition and Preprocessing

Resting state functional MRI data and 3D high-dimension T1 image will be collected using a 3T Siemens Magnetom Prisma MRI scanner. PD patients will take medication during MRI scanning to minimize movement artifacts and reduce discomfort. All participants will be instructed to keep their eyes open and focus on a white “+” on black screen, letting their minds wander and trying not to fall asleep during the 10 min 6 s resting state functional MRI scan (gradient echo/fast gradient echo pulse sequence: repetition time = 2000 ms; echo time = 30 ms; flip angle = 80°; matrix size = 106 × 106; number of slices = 62; and voxel size = 2.0 × 2.0 × 2.0 mm^3^ with no gap; number of total volume = 304). During the structural scan participants will be instructed to sleep (repetition time = 3130 ms; echo time = 2.98 ms; flip angle = 4°; matrix size = 256 × 256; number of slice = 176; voxel size = 1.0 × 1.0 × 1.0 mm^3^).

Data preprocessing will be conducted using the SPM12 package implemented in MATLAB R2019a^1^. Prior to preprocessing (1) the first four scans will be deleted from the resting functional volume; (2) functional scans will be realigned to the first volume to correct for interscan head motion; (3) functional scans will be segmented into gray matter, white matter, and cerebrospinal fluid using the Tissue Probability Map template; and finally, and (4) normalized into standard Montreal Neurological Institute space using non-linear transformations and spatially smoothed with a Gaussian smoothing kernel of 6 mm. Participants with head motion greater than 1 mm will be removed from the study (Liao et al., 2014).

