#### Dynamic functional connectivity

##### Sliding Window Approach

Sliding window analysis will be applied using the DFC network toolbox in GIFT. Resting state data will be separated into windows of 22 repetition times (44 s), and the regularized inverse covariance matrix will be used as covariance estimation using shorter time series can be noisy. An additional L1 norm of the precision matrix will be imposed to promote sparsity in the graphic LASSO framework with 100 repetitions. Subsequently, the functional connectivity matrices will be transformed to z-scores using Fisher’s z-transformation and covariates (age, gender, and education) will be regressed out.

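### Head motion below the 1 mm cut-off is neither removed nor adjusted for in the listed DFC analysis, which may confound the temporal measures, chiefly in the non-randomised PD versus HC comparison

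*Protocol article*

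**What the plan says.** All references are to the protocol article.

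- **Resting-State and Structural MRI Acquisition and Preprocessing.** The pipeline is given step by step. The first four volumes are dropped, then "functional scans will be realigned to the first volume to correct for interscan head motion". The scans are next segmented, and finally "normalized into standard Montreal Neurological Institute space using non-linear transformations and spatially smoothed with a Gaussian smoothing kernel of 6 mm". Two further motion controls follow from the same section: "Participants with head motion greater than 1 mm will be removed from the study", and "PD patients will take medication during MRI scanning to minimize movement artifacts and reduce discomfort".
- **Group Independent Component Analysis.** Components are kept if their reliability exceeds 0.80. No artefact criterion is listed.
- **Sliding Window Approach.** Connectivity is estimated in windows of 22 volumes (44 s) with L1 regularisation. After Fisher's transformation, "covariates (age, gender, and education) will be regressed out".
- **Group differences in dynamic connectivity**, under both the replication heading (PD versus HC) and the Wuqinxi application heading (arm comparison). The same sentence appears in each: "Covariates will include education, levodopa and dopamine agonist equivalent daily doses".
- **Sample Size Calculation and Blinding.** Recruitment is set at 40 per PD arm and 40 HC, above the calculated 22 per arm, because "some participants may need to be dropped from the analysis due to excessive head motion during scanning".
- **Discussion.** Dopaminergic therapy and mood are named as possible influences on functional connectivity. Head motion is not.

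**The concern.** Realignment repositions the images; it does not take motion-related signal out of the time courses. An exclusion threshold removes the worst scans but leaves all motion below it in the data, and it does not make that remaining motion equal between groups.

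The temporal DFC measures are exposed to this. If windows advance one volume at a time (the step is not stated, so this is an assumption), one disturbed volume enters up to 22 successive windows. With the two states the article fixes, a single artefactual excursion and return would add two transitions and cut short a dwell period.

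PD versus HC is a non-randomised comparison involving a movement disorder, so a motion difference among retained scans is plausible. Design and Procedures gives this comparison a particular job: to support use of the DFC method in these participants before it is applied to the intervention. A difference produced by motion would look like a successful replication and weaken what is built on it.

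**Working it through.** **1. The plan's own figure.** The only related figure is the minimum sample size of 44. Inputs from Sample Size Calculation and Blinding: f = 0.25, alpha = 0.05, power = 0.95, two groups; three timepoints from the analysis section. Assumed, as not stated: correlation 0.5 between repeated measures, and sphericity.

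- Noncentrality = f² × N × m / (1 − rho) = 0.0625 × 44 × 3 / 0.5 = 16.5, with 2 and (44 − 2) × 2 = 84 degrees of freedom.
- Power is 0.956 at N = 44 and 0.946 at N = 42, so 44 reproduces.
- Losing one subject-level degree of freedom to a motion covariate changes power from 0.9557 to 0.9556 at N = 44, and leaves it at 0.9991 at N = 80. This counts lost degrees of freedom only.

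**2. Where motion is handled.**

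| Place | What is listed | Motion term? |
|---|---|---|
| Acquisition | PD scans on medication | Limits motion; no adjustment |
| Preprocessing | Realignment; 1 mm exclusion | Gross motion only |
| Component selection | Reliability > 0.80 | No |
| Windowed matrices | Age, gender, education | No |
| PD versus HC model | Education, dopaminergic doses | No |
| Arm model | Education, dopaminergic doses | No |

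**3. Possible size.** Nothing in the article gives the motion difference or its correlation with a DFC measure; both are assumed.

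- Spurious standardised difference = (motion difference in SD) × (correlation of motion with the measure).
- Noncentrality = spurious difference / √(1/n₁ + 1/n₂), two-sided t test at 0.05 (two-sidedness assumed).
- Example, 80 versus 40: √(1/80 + 1/40) = 0.1936. With 0.5 SD and r = 0.3 the spurious difference is 0.15 and the noncentrality 0.15 / 0.1936 = 0.77, giving 12.0% rejection.

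Rejection rates under no true effect, per test, before FDR:

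| Motion difference (SD) | r | Spurious d | PD–HC, 80 v 40 | PD–HC, 44 v 22 | Arms, 40 v 40 |
|---|---|---|---|---|---|
| 0.2 | 0.1 | 0.02 | 5.1% | 5.1% | 5.1% |
| 0.3 | 0.2 | 0.06 | 6.1% | 5.6% | 5.8% |
| 0.5 | 0.3 | 0.15 | 12.0% | 8.7% | 10.2% |
| 0.8 | 0.4 | 0.32 | 37.4% | 22.7% | 29.3% |

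The 80 v 40 column assumes every scan is retained. The 44 v 22 column is an illustrative retention (44 is the stated PD minimum; 22 HC is assumed). The arms column is a t test at one timepoint, not the planned arm-by-time interaction, and applies only if motion has diverged between arms by the amount shown.

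**The case against.** **The article is condensed.** Nuisance regression or artefact-component screening may be set out in a fuller document, and the article says it will first follow the methods of two earlier DFC studies, which cannot be seen here. This stands in part. A reader might infer that the trial will do no motion denoising; the text supports only that none is listed. It does not answer the covariate lists, which are explicit in three places and omit motion.

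**Motion is already controlled.** Realignment is not the end of preprocessing: segmentation, normalisation, smoothing and the 1 mm exclusion follow, and patients are scanned on medication. Regularised covariance also guards against noisy short windows. A reader might infer that motion goes uncontrolled, or that the sponsor expects it to be a major problem; the article says only that some participants may be dropped. These measures limit gross motion, but none adjusts for what remains.

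**The treatment comparison is randomised.** A reader might infer that the Wuqinxi versus balance result is biased. The documents do not support that. Randomisation balances motion in expectation, and the arm-by-time interaction removes stable differences between people. Bias would need motion to change differently by arm, or unequal exclusion after randomisation. The first is conceivable, since the stated hypothesis includes a change in motor impairment, but nothing in the article shows either. Motion after treatment is also a post-randomisation variable, so adjusting for it may change the effect being estimated. This objection stands and limits what should change in the arm analysis.

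**The size is assumed.** This also stands. The figures ignore FDR and, at 80 versus 40, the very exclusions the sample size allows for.

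**Conclusion.** The point holds, with its weight on PD versus HC. Beyond realignment, the 1 mm exclusion and on-medication scanning, no listed step removes motion-related signal and no listed covariate represents it. Motion below the cut-off may therefore confound dwell time, fractional windows and transitions in that comparison. Between the randomised arms it is a secondary risk that calls for reporting and a sensitivity analysis.

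The size runs from negligible to material and rests entirely on assumed inputs. Over motion differences of 0.3 to 0.8 SD and correlations of 0.2 to 0.4, per-test type I error before FDR is about 6% to 37% at 80 versus 40, and about 6% to 23% at the illustrative 44 versus 22. These figures are not estimates of this trial's error rate. The change is worth making because it is cheap and the measures are primary outcomes; confidence is medium.

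**What to change.** 1. **Preprocessing section:** state that the realignment parameters and their derivatives will be regressed out of the component time courses before windowing. If a fuller document already specifies this, refer to it.
2. **Group differences, PD versus HC:** add mean framewise displacement of the scan to the covariates, and report it by group.
3. **Group differences, Wuqinxi versus balance:** keep the planned model as primary. Report mean framewise displacement by arm and visit, and show a motion-adjusted model as a sensitivity analysis. Use a mixed model for it, because the covariate varies by visit and does not fit simply into the planned repeated ANOVA.

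The cost is wording and a little analysis time, since realignment already yields the parameters. The PD versus HC model gives up one degree of freedom, out of 80 + 40 − 2 = 118 before other covariates at full retention. The real downside is that true signal tracking motion may be removed, so the PD versus HC result without the motion term should be shown as a sensitivity analysis.
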